#### Secondary outcome measurements

Gluteus medius muscle activity, transversus abdominis muscle thickness and foot type will be assessed as outlined in Table 1. Physical activity will be assessed using the IPAQ-7 which consists of seven questions about the amount and intensity of moderate and vigorous physical activity undertaken in the past 7 days, as well as, the amount of time spent sitting [56]. The diary provided to participants in the prefabricated foot orthotic group will be used by participants to record the number of hours per day they have worn the orthotic device over 12 weeks. In addition to participants being able to contact the researchers at any stage of the trial to report adverse events, they will be asked if such events have occurred at the face to face follow-up session at 12 weeks.

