### Interventions

Participants in the control group will receive ‘The Back Book’ educational booklet (Additional file 1) which contains written information about techniques for dealing with back pain. It has been demonstrated that this booklet has no significant effect on improving pain or function in people with chronic nonspecific LBP [31].

The intervention group will also receive ‘The Back Book’. In addition, they will be issued a pair of Formthotics™ prefabricated foot orthoses (Foot Science International Ltd., Christchurch, New Zealand, Fig. 2). The prefabricated foot orthoses will be heat moulded to fit the participant’s feet as per the manufacturer’s instructions. The devices will be worn in the participant’s usual footwear for 1 year from baseline. Wearing in instructions will be provided by the therapist (registered podiatrist), issuing the intervention. During the fitting process participants are shown, by the therapist, how the devices are fitted to their footwear. Participants are instructed to wear the devices as much as possible and that they may change them to other suitable shoes. Shoe suitability will be discussed as part of the fitting process. Participants in the prefabricated orthotic group will be provided with a usage diary. This and each intervention will be provided to participants by the therapist who is located in a separate room, after baseline questionnaires and clinical measurements are completed.

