### Data collection sessions

Participants will be required to attend two data collection sessions: baseline and 12 weeks later (Fig. 1). Follow-up questionnaires will be mailed to participants at 26 and 52 weeks after the baseline session.

After the GP has screened a participant and they have contacted the researcher for phone screening, a baseline testing session will be arranged, and they will be sent a general health questionnaire which they will be asked to bring completed to the baseline testing session. The general health questionnaire consists of questions about sociodemographic variables. During the phone screening, potential participants will be asked about current and previous treatments for their LBP and instructed to wear suitable attire for clinical testing and to bring multiple pairs of lace-up or Velcro, enclosed footwear.

The assessor ([name]), who will be blinded to treatment allocation, will conduct baseline and follow-up anthropometric and clinical measurements, and issue self-administered baseline and follow-up questionnaires to participants.

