### Follow-up sessions (12, 26 ad 52 weeks)

Participants will be required to return 12 weeks after the baseline testing session to have their gluteus medius muscle activity and transversus abdominis muscle thickness remeasured. Participants will also be required to complete the numeric pain rating scale, Oswestry Disability Index, and International Physical Activity Questionnaire (IPAQ-7). Participants will also be mailed these questionnaires 26 and 52 weeks after baseline testing. At the 12 week follow-up, participants will be asked if they have read ‘The Back Book’. The participant information statements contain the researchers’ contact details so participants can report adverse events at any stage of the trial. Adverse events will be managed by the researchers or participants will be referred to their GP.

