### Secondary outcomes

The secondary outcomes will include:(i)Gluteus medius muscle activity from baseline to 12 weeks follow-up;(ii)Transversus abdominis muscle thickness from baseline to 12 weeks follow-up;(iii)correlation between foot type and change in pain and function;(iv)physical activity from baseline to 12, 26, and 52 weeks follow-up;(v)number of hours per day and week the prefabricated orthotic is worn over 12 weeks; and(vi)self-reported adverse events associated with the interventions over 52 weeks.

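### Adverse events are a 52-week outcome, but the only active enquiry described is at week 12, so the last 40 weeks rest on participant-initiated reports

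*Protocol article*

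**What the plan says.** Under Secondary outcomes, the last of six items is "self-reported adverse events associated with the interventions over 52 weeks". Under Interventions, the orthoses are to be worn in the participant's "usual footwear for 1 year from baseline". The outcome window and the planned device exposure are therefore both one year.

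Two ways of learning about events are described. The first is passive: under Follow-up sessions, the information statements carry the researchers' "contact details so participants can report adverse events at any stage of the trial". The second is active: under Secondary outcome measurements, participants can make contact at any time and, in addition, "they will be asked if such events have occurred at the face to face follow-up session at 12 weeks".

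The contact schedule is stated under Data collection sessions: "Participants will be required to attend two data collection sessions: baseline and 12 weeks later". Everything later is by post. Follow-up sessions lists the numeric pain rating scale, Oswestry Disability Index and IPAQ-7 for week 12 and continues: "Participants will also be mailed these questionnaires 26 and 52 weeks after baseline testing". The orthosis group also keeps a diary, in which they "record the number of hours per day they have worn the orthotic device over 12 weeks".

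**The concern.** The ascertainment method does not match the outcome window. Up to week 12, events are elicited by a direct question. From then to week 52, on the text as it stands, an event enters the data only if the participant takes the initiative. Events that are volunteered are usually fewer than events that are asked about, and minor ones are the most likely to be lost.

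Two things are at stake. A 52-week count would probably be too low by an unknown amount. The periods before and after week 12 would also rest on different methods, so a lower rate in the second period could reflect the change of method rather than better tolerance. The Discussion already says that earlier research with these orthoses reported few adverse events. A low count here could be taken to confirm that when part of it comes from not asking.

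This goes beyond detail left to a fuller document. The article states when the question is put and names the instruments that are mailed.

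**Working it through.** The article gives no adverse-event figure to reproduce. The check sets the stated contacts against the outcome window and then shows how much could be lost.

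**Inputs from the article**
- Outcome window: 52 weeks (Secondary outcomes).
- Planned device wear: 1 year, intervention arm (Interventions).
- Attended sessions: baseline and week 12 (Data collection sessions).
- Active enquiry: one, at week 12 (Secondary outcome measurements).
- Later contacts: questionnaires mailed at weeks 26 and 52, named as pain scale, Oswestry and IPAQ-7 (Follow-up sessions).
- Diary: hours of wear, 12 weeks, orthosis group only (Secondary outcome measurements). It is not described as an adverse-event record and it stops at week 12.

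**Contacts side by side**

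| Period | Described contact at end of period | Adverse-event question described? |
|---|---|---|
| Weeks 0–12 | Face-to-face visit | Yes |
| Weeks 12–26 | Mailed questionnaires | No |
| Weeks 26–52 | Mailed questionnaires | No |

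Time after the only active enquiry: 52 − 12 = 40 weeks, and 40/52 = 76.9%. The reporting gap applies to both arms; the 40 weeks of device exposure apply to the intervention arm.

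**Illustration (assumptions not in the article)**

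Let f be the share of all events that arise by week 12, and p the share of later events that participants volunteer. Assume every event up to week 12 is captured. Then

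capture = f + (1 − f) × p, and loss = (1 − f) × (1 − p).

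If events arise evenly over the year, f = 12/52 = 0.231 and 1 − f = 40/52 = 0.769:

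| p | Capture | Loss |
|---|---|---|
| 0.30 | 0.231 + 0.769 × 0.30 = 46% | 54% |
| 0.50 | 0.231 + 0.769 × 0.50 = 62% | 38% |
| 0.70 | 0.231 + 0.769 × 0.70 = 77% | 23% |

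The loss shrinks as f rises and is zero if every event falls in the first 12 weeks. The table therefore shows sensitivity to p under an even spread and is not an estimate for this trial.

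**After the fix**

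With the question on both mailed forms, the time with no later enquiry falls from 40 of 52 weeks to 0 of 52 for participants who return both. The recall windows become 12, 26 − 12 = 14 and 52 − 26 = 26 weeks.

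**The case against.** The strongest reply is that nothing here is contradictory. The outcome is labelled self-reported, and a self-report route is open throughout the trial, so a 52-week outcome has a 52-week channel. That stands: the point concerns weak and uneven ascertainment and is not an internal contradiction.

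The second reply is that the lists in the article are not exhaustive. The week-12 list under Follow-up sessions omits the adverse-event question that Secondary outcome measurements places at that visit. The Discussion promises to record external treatments without naming a form. A reader might infer that the mailed packs hold only the three named instruments, but the article does not say so, and a fuller protocol could hold an item that is not shown. What remains is that the article does describe how adverse events are sought, and ties the active question to week 12 alone.

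Three other stronger readings go beyond the text:

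- **That later events are recorded only if someone telephones.** The article says participants can contact the researchers and gives no mode.
- **That participants, knowing their treatment, decide whether an event was caused by it.** The outcome is limited to events associated with the interventions, but self-reported says who reports, not who judges cause. No section assigns attribution. The two-level information statements are also meant to keep participants unaware of the other arm's treatment.
- **That the trial would probably record no late events at all.** Suppose 10% of 30 orthosis users have a late event. At 30% volunteering the chance of recording none is (1 − 0.10 × 0.30)^30 = 40%, against (1 − 0.10 × 0.80)^30 = 8% if 80% of events are captured by asking. At 70% volunteering it is (1 − 0.10 × 0.70)^30 = 11%, close to the 8%. The contrast depends almost wholly on assumed rates.

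It is also fair to say that 77% is a share of calendar time and not of events. The wearing-in instructions make early clustering plausible, though the article gives no timing of events. No comparison of the 12-week and 52-week rates is planned in the article.

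**Conclusion.** The point holds as a mismatch between a 52-week outcome and an ascertainment method whose only described active enquiry is at week 12. For 40 of 52 weeks (77% of calendar time), events are recorded, as written, only if participants contact the researchers. Under-counting after week 12 is likely but not certain, and its size cannot be derived from the article. Under the even-spread assumption, overall capture runs from about 46% to 77% as the volunteered share runs from 30% to 70%; with early clustering the loss is smaller.

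The conclusion assumes that no adverse-event item is added to the mailed forms in a document not shown. It bears on one secondary outcome and leaves the primary outcomes, their analysis and the sample size untouched. The change is worth making because it is cheap and because the 52-week count is hard to interpret without it.

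**What to change.** Add the adverse-event question asked at week 12 to the questionnaires mailed at weeks 26 and 52, in both arms. Use the same wording at all three times, and ask about any new or worse symptom since the last enquiry, whatever the participant thinks caused it. Any judgement of relatedness can then be made separately, and the arms can be compared without it. Report events by arm and by period (0–12, 12–26, 26–52 weeks), keeping elicited and spontaneous reports apart. If the fuller protocol already has such an item, stating so under Secondary outcome measurements is enough.

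The cost is one item on two existing mailings, a slightly longer form and a minor ethics notification. Two limits remain: participants who do not return a form are still covered only by spontaneous reports, and the last recall window is 26 weeks, so minor events may still be forgotten.

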### Sample size

The sample size for this trial was calculated to find minimal clinically important change of 2 (s = 2.5) on the numeric pain rating scale [29] with 80% power, a 5% Type I error rate and non-adherence rate of 20%. Numeric pain rating scale was chosen for the calculation instead of the Oswestry Disability Index because it had the smaller effect size and thus would require the larger sample size. The calculation adjusted for non-adherence required a total sample size of 30 per group, therefore a total of 60 participants will be recruited.

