## Methods

### Design

This is a two-armed, parallel-group (intervention versus control), participant and assessor blinded superiority randomised (1:1) controlled trial (Fig. 1). Allocation concealment will be used to prevent selection bias by the use of sequentially numbered, opaque sealed envelopes containing a permuted block random allocation schedule with mixed block lengths of four and six participants. The trial will be conducted at the University of Newcastle Ourimbah Campus and the Podiatry Clinic at Wyong Hospital, both located in NSW, Australia. The trial has been prospectively registered on the Australian New Zealand Clinical Trials Registry (ACTRN12618001298202). The results of this trial will be reported using the CONSORT statement [28].

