### Statistical and data analysis

Statistical analysis will be conducted using the latest version of appropriate statistical software (e.g. SPSS or STATA). Analyses involving primary outcomes will be conducted on an intention-to-treat principle using all randomised participants. Missing data will be replaced using multiple imputation. Normality will be assessed using the Shapiro Wilks test. For the primary outcomes of pain and function (numeric pain rating scale and Oswestry Disability Index), data will be compared using analysis of covariance (ANCOVA) to investigate the change from baseline to each of the follow-up points. The baseline measure will be the only covariate used in each analysis.

The IPAQ-7 will be used to determine changes in physical activity from baseline for participants using analysis of covariance at each time point (12, 26 and 52 weeks). The correlation between IPAQ-7 score and change in primary outcomes will be investigated and where appropriate (significant correlations identified) a regression analysis performed. For the secondary outcomes of gluteus medius activity and transversus abdominis thickness, ANCOVA will be used to investigate change from baseline following 12 weeks of the intervention for each variable. The baseline measure will be the only covariate used in each analysis. Cohen’s d will used to calculate effect sizes for both primary and secondary outcomes.

Pearson correlation coefficients will be performed between foot type and the change in primary outcome variables at 12, 26, and 52 weeks. Where significant correlations are found, a regression analysis will then be performed to determine the ability of foot type to predict treatment outcomes.

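### The 30 per group treats 20% non-adherence as lost participants, but the ITT analysis keeps them, so the claimed 80% power is not supported as written

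*Protocol article*

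**What the plan says.** The Sample size section of the protocol article sizes the trial on pain, for a "minimal clinically important change of 2 (s = 2.5) on the numeric pain rating scale", "with 80% power, a 5% Type I error rate and non-adherence rate of 20" per cent. It concludes: "The calculation adjusted for non-adherence required a total sample size of 30 per group, therefore a total of 60 participants will be recruited". It shows neither the unadjusted number nor the inflation formula. It does not say whether 2.5 is the SD of the score, of the change or of the ANCOVA residual, and it does not say whether the 5% is one- or two-sided.

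The Statistical and data analysis section says: "Analyses involving primary outcomes will be conducted on an intention-to-treat principle using all randomised participants". Missing values are multiply imputed, and each follow-up is analysed by ANCOVA with baseline as the only covariate. No baseline–follow-up correlation is given.

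Under Interventions, both arms receive the booklet and only the intervention arm receives orthoses. The Primary outcomes section makes 12 weeks the primary time point.

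**The concern.** An adjustment that multiplies up the number of participants suits people whose outcomes are not available for analysis. Non-adherers under an intention-to-treat analysis are a different case: they are measured and analysed, and what shrinks is the average difference between arms. The Sample size section appears to use the first kind of adjustment for a quantity that it names as the second kind.

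At stake is how a null result on pain would be read. The paragraph tells the reader that the trial has 80% power after allowing for 20% non-adherence. If the power of the planned analysis is lower, a non-significant result is weaker evidence against a 2-point effect than the paragraph implies.

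**Working it through.** **Inputs.** From the Sample size section: difference 2, SD 2.5, power 80%, type I error 5%, non-adherence 20%, 30 per group. From the Design section: 1:1 allocation. Assumption: the 5% is two-sided. A one-sided test needs 20 per arm, which inflates to 24 or 25 and does not reproduce 30.

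**Step 1. Reproduce the stated figure.**
- Unadjusted: n = 2 × (1.960 + 0.842)² × (2.5/2)² = 24.5, so 25 per arm. The t-test needs 26.
- 25 × 1.2 = 30, an exact match.
- Allowing for 20% loss by division: 25/0.8 = 31.25, so 32 per arm; 26/0.8 = 32.5, so 33 per arm.
- The ×1.2 route is inferred. Truncating 24.53/0.8 = 30.66 also gives 30. Both routes treat the 20% as removed from the analysis.

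**Step 2. The 20% as lost outcomes.** 30 × 0.8 = 24 per arm remain. At a difference of 2 and SD 2.5, power is 79.1% (normal approximation) or 77.4% (noncentral t). The inflation slip therefore costs about 1 to 3 points.

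**Step 3. The 20% as non-adherence kept under ITT.** Only the orthosis arm can fail to wear orthoses. If non-adherers keep a fraction f of the benefit, the ITT difference is 2 × (0.8 + 0.2f). At 30 per arm and SD 2.5:

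| Benefit kept by non-adherers | ITT difference | Power, normal | Power, t |
|---|---|---|---|
| None (f = 0) | 1.6 | 69.8% | 68.4% |
| Half (f = 0.5) | 1.8 | 79.6% | 78.3% |
| All (no dilution) | 2.0 | 87.3% | 86.1% |

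Power reaches 80% when non-adherers keep about 52% of the benefit (normal) or about 60% (t). With f = 0, 80% power would need 39 per arm (normal) or 40 (t).

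**Step 4. Possible gain from ANCOVA.** If 2.5 is the raw SD of the follow-up score, the residual SD is 2.5 × √(1 − r²), where r is the baseline–follow-up correlation. For full dilution (difference 1.6) and 30 per arm, t-based power is 68% at r = 0, 72% at r = 0.3, 80% at r = 0.5 and 86% at r = 0.6. If 2.5 is already the residual SD, there is no such gain.

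**The case against.** Four points on the other side have force.

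- **The arithmetic slip is small and inferred.** Two participants per arm separate 30 from 32, and the article shows no formula. This stands, and the multiplication by 1.2 would not by itself justify more than a correction.
- **Non-adherence may have meant non-completion.** The 20% is applied to both groups although only one has orthoses to wear, which fits loss of participants at least as well. On that reading the shortfall is only the 1 to 3 points of step 2. The paragraph would still need to say so, and actual non-wear would then have no allowance.
- **The 68–70% is the unfavourable end.** It assumes that non-adherers gain nothing, although wear is recorded in hours and partial wearers may benefit. It also takes 2 points as the effect under full adherence. If 2 points is the target for the ITT contrast itself, no dilution applies and power is 86–87%. The paragraph's own non-adherence adjustment makes that reading less natural but does not exclude it.
- **ANCOVA may recover the loss.** A correlation of about 0.5 would do so if 2.5 is a raw SD. This is plausible, but the protocol states no correlation and claims no gain, so it cannot be credited to the stated calculation.

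A reader might infer more than this. One inference is that the trial certainly has less than 80% power; the documents do not settle that, because the answer turns on the unstated assumptions above. Another is to apply a 20% loss on top of 20% non-adherence; the protocol gives a single 20%, and using it twice has no basis in the text. A third is that nothing is left for attrition over a year of mailed questionnaires; the power claim belongs to the 12-week primary time point, which is an attended session, and questionnaires are mailed only at 26 and 52 weeks.

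**Conclusion.** The point holds as an inconsistency between the Sample size section and the analysis set. The paragraph presents 80% power after adjustment for 20% non-adherence, but the adjustment that reproduces its figure is one for removed participants, and the primary analysis removes nobody.

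At 30 per arm, on the stated inputs with no ANCOVA gain, power runs from about 68% to 87% according to what the 20% means and how much benefit non-adherers keep. The two plain readings, 20% lost and 20% non-adherent with no benefit, both fall below 80%: slightly in the first case and by about 10 to 12 points in the second. These figures assume a two-sided test and treat 2.5 as the SD that applies in the analysis.

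This is a should-fix. The design and the planned analysis can stand; the power statement cannot stand as worded.

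**What to change.** Keep 60 participants and rewrite the Sample size paragraph so that it:

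1. gives the unadjusted need of 25 per arm (26 by t-test) and states that the 5% is two-sided, if that is what was intended;
2. says whether the 20% is non-adherence or loss to follow-up;
3. uses division by 0.8 for any allowance for lost outcomes;
4. reports power at 30 per arm for the 12-week comparison separately for 20% missing outcomes (about 77–79%) and for 20% non-adherence under ITT (about 68–70% with no residual benefit, 78–80% with half), stating the residual benefit assumed;
5. says which SD 2.5 is and, if ANCOVA gain is relied on, gives the correlation and the resulting power;
6. no longer describes 60 as giving 80% power after adjustment for non-adherence.

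The cost is one reworded paragraph and a less favourable or more conditional power statement. No extra participants and no change to the analysis are needed.
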